
### 3.3. Electromyographic Equipment

This study will require a Surface Electromyographer, a bioamplifier (EMG Brainquiry Personal Efficiency Trainer^®^: PET 4, Brainquiry, Nijmegen, The Netherlands) and pre-gelled adhesive electrodes with a hook-and-loop of 18 mm. Furthermore, it requires a chair for the patient, a table, and a screen to display videos. The recordings will be digitised using 55 Hz high-pass filtering and stored in raw form. The Average Rectified Value (ARV) and Root Mean Square (RMS) of the obtained data will be determined for amplitude, and the Median Frequency (MNF) and Mean Power Frequency (MDF) will be determined for frequency. Subsequently, the electromyographic power of the target contractile events will be assessed after discrimination of possible recording interferences and artefacts. The contractile activity shall be considered when the electromyographic signal exceeds the mean plus two standard deviations in the baseline activity of each muscle for at least 100 ms.

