## 1. Introduction

Acquired Brain Injury (ABI) is defined as a sudden injury to the brain, classified as an ischemic stroke (blockage of a blood vessel) or haemorrhagic stroke (rupture of a blood vessel) [1]. The increases in life expectancy and healthcare quality have increased the number of survivors affected by stroke [2,3]. This situation will increase costs associated with service provision and loss of productivity, making studying rehabilitative techniques for improved functional recovery essential.

People who have suffered a stroke may have physical, cognitive, emotional, and social sequelae that alter their functionality and quality of life. Many of these people suffer motor impairments at the level of the upper limbs, which implies severe difficulties in performing activities of daily living (ADLs) [4]. Improving the indication of treatment tools will allow better results to be achieved in increasing these people’s functionality and quality of life.

Rizzolatti’s discovery of mirror neurons in the 1990s was a significant breakthrough in neurorehabilitation [5], as new tools and therapeutic approaches based on neuroplasticity mechanisms appeared. In these tools, the focus is on achieving more direct brain stimulation, achieving motor relearning through the mechanisms of neuronal plasticity. Motor imagery (MI) and action observation (AO) are some of the techniques in this approach. In contrast, other more traditional techniques derived from the bottom-up approach seek to act at the physical level and produce changes at the central nervous system level, such as Vojta or Bobath therapy [6].

MI involves the cognitive task of imagining the realisation of the movement without physically executing it. It is based on the use of cognitive and perceptual processes that results in neural activation similar to that which occurs when the actual execution of the movement or task is performed [7]. Its efficacy in activating cortical and subcortical areas has been demonstrated [8]. However, more evidence must be presented regarding the motor response it elicits. In addition to knowing that the brain areas that are activated during MI are areas related to motor planning, programming, and execution [9], it is of great interest to know the degree of muscle activation and what individual characteristics or determinants modify it during neurorehabilitation.

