### 2.3. Participants

The study will be carried out on a population of adults with stroke. Subjects will be recruited by convenience sampling through the Rehabilitation Service of the University Hospital of Salamanca and the Salamanca Association of Acquired Brain Injury (ASDACE). Subjects will be asked to participate voluntarily in the study, and once the objectives and content have been explained, they will sign the corresponding informed consent form.

The inclusion criteria are:Being over 18 years of age with an established diagnosis of stroke.Presenting motor response limitations or deficiencies in the upper limbs.Maintaining cognitive functions with the capacity to follow the indications of the interventions and assessments in Spanish language (The Montreal Cognitive Assessment, MoCA > 14).

The following exclusion criteria will be considered: having been diagnosed with mental illness before the stroke; presenting with central nervous system conditions other than stroke or severe or acute cardiorespiratory system disorders; and presenting with fever, muscle inflammation, or myopathies, as well as any vascular and organic insufficiency, liver disease, or skin lesions in the area of application of the electrodes.

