### 3.4. Videos

Two recordings of identical durations will be available to compare the EMG recordings under each condition. Recording 1 will show images of landscapes without the presence of any person or animal and will be used for the control condition. Recording 2 will be based on the activities of the CEMIMA. In this recording, three activities will be visualised: opening and closing the hand, throwing and catching a tennis ball, pouring sugar into a coffee cup and stirring (Figure 1). The first minute of both recordings will serve as the resting time, which is essential for later analysis of the results. Recordings will be available in the open access repository for the research community once the study is finished.

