## 4. Detailed Procedure

### 4.1. Experimental Conditions

The study participants will take part in three sessions, one session per week, and in each one, different experimental conditions will be used: experimental control conditions, experimental MI conditions and experimental AO conditions (Figure 2). In the first session, the socio-clinical-demographic data of all participants will be collected.

Recording 1 will be used during the control experiments and Recording 2 will be used in the MI and AO experiments (Figure 2); in the first case, the Spanish audio of the recording will be used, and in the second case, the images will be used. The first minute of both recordings will serve as a resting time, which is essential for subsequent analysis of the results.

During all three experiments, subjects will be seated in front of a stretcher on which they will rest their forearms with their elbows in slight flexion. Before the first experimental condition, socio-clinical-demographic data will be collected for the different assessment tools.

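### The EMG event rule cannot separate covert activation from executed hand movement, so overt copying during MI or AO would be scored as a response to imagery or observation

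*Protocol article*

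**What the plan says.** **The scoring rule (section 3.3).** "The contractile activity shall be considered when the electromyographic signal exceeds the mean plus two standard deviations in the baseline activity of each muscle", and this must last "for at least 100 ms". Before that, "the electromyographic power of the target contractile events will be assessed after discrimination of possible recording interferences and artefacts". The rule has a lower amplitude bound and a minimum duration. It has no upper bound and no criterion that refers to movement.

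**The construct (Introduction).** "MI involves the cognitive task of imagining the realisation of the movement without physically executing it". AO is described there as watching a video; performing the action is mentioned as a usual later step, not as part of the observation.

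**The participants (section 2.3).** The motor criterion is "Presenting motor response limitations or deficiencies in the upper limbs". No ceiling is set on residual function.

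**The stimuli and posture (sections 3.4 and 4.1).** The recording used for MI (audio) and AO (images) presents "opening and closing the hand, throwing and catching a tennis ball, pouring sugar into a coffee cup and stirring". The control recording shows landscapes without people or animals. In all three conditions participants sit in front of a stretcher "on which they will rest their forearms with their elbows in slight flexion".

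**The inference (section 5).** The study is to test whether MI and AO activate the wrist and finger muscles, and whether that activation relates to factors such as upper-limb function.

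**The concern.** By the article's own definition, a participant who opens and closes the hand during the MI recording is not doing MI. The rule still scores that contraction as an MI response. The artefact step does not help, because a voluntary contraction is genuine muscle signal.

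The control condition cannot subtract the error, since it gives no cue to move the hand. Any copying would fall mainly in MI and AO and push both contrasts towards activation.

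People with better arm function are also more able to copy. Copying could therefore produce the association between EMG response and upper-limb function that the fourth secondary objective looks for, without any effect of imagery or observation.

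**Working it through.** **Does an executed movement pass the rule?**

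| Element of section 3.3 | Executed finger movement |
|---|---|
| Above baseline mean + 2 SD | Met: the recorded muscles are finger flexors and extensors |
| At least 100 ms | Met by any ordinary hand movement |
| Interference and artefacts discriminated first | Not removed: it is true EMG |
| Upper limit or movement criterion | None stated |

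So the rule gives the same score to covert activation and to execution.

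**How large could the effect be?** The plan gives no figure on this point. From the documents I take n = 21 to 28 (section 2.4) and alpha 0.05 (section 4.3). The test is assumed two-sided, so the nominal rate of false activation is 2.5%. All other inputs are assumptions:

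- share of participants who move, q: 5% to 35%
- movement amplitude, k: 5 to 10 times resting RMS
- share of task time spent moving, t: 1% to 5%
- SD of the log ratio of task to reference RMS: 0.2 to 0.4
- true effect of imagery or observation: zero

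A mover's RMS is multiplied by sqrt(1 − t + t·k²):

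- k = 10, t = 0.05: sqrt(0.95 + 0.05 × 100) = 2.44, log 0.892
- k = 5, t = 0.01: sqrt(0.99 + 0.01 × 25) = 1.11, log 0.108

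Each simulated log ratio is Normal(0, SD), plus the log inflation with probability q. A one-sample t-test is then applied. Share of trials significant for activation (40,000 trials per cell):

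| Movers | k | t | SD | n = 21 | n = 28 |
|---|---|---|---|---|---|
| 35% | 10 | 5% | 0.2 | 86% | 95% |
| 25% | 10 | 5% | 0.2 | 62% | 78% |
| 15% | 10 | 5% | 0.2 | 28% | 41% |
| 15% | 10 | 5% | 0.4 | 18% | 25% |
| 15% | 10 | 1% | 0.2 | 15% | 19% |
| 15% | 5 | 5% | 0.4 | 9% | 10% |
| 5% | 10 | 5% | 0.2 | 6% | 8% |
| 15% | 5 | 1% | 0.2 | 6% | 6% |
| 5% | 5 | 1% | 0.4 | 3% | 3% |

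This is a test on whole-task RMS. It is not the event rule, and the article fixes no such test.

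**An illustration closer to the event rule.** Score each participant as having a response or not, and assume that only movers differ between MI or AO and control. With m movers, the two-sided exact sign test gives p = 2 × 0.5^m:

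- m = 5: p = 0.063
- m = 6: p = 0.031

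Six movers are 29% of 21 or 21% of 28. If 10% / 20% / 30% of participants move, the chance of at least six movers is 1.4% / 23% / 64% at n = 21 and 5.5% / 50% / 89% at n = 28.

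**Association with arm function.** Assume 25% move and movers average 1 SD better arm function. The mover indicator has variance 0.25 × 0.75 = 0.1875.

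- k = 10, t = 5%, SD 0.2: r = (0.892 × 0.1875) / sqrt[(0.04 + 0.892² × 0.1875) × (1 + 0.1875)] = 0.167 / 0.474 = 0.35
- k = 5, t = 1%, SD 0.4: r = (0.108 × 0.1875) / sqrt[(0.16 + 0.108² × 0.1875) × 1.1875] = 0.020 / 0.439 = 0.05

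The spurious correlation thus runs from negligible to moderate.

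**The case against.** **A condensed article may leave out participant instructions and operator checks.** This stands as far as it goes: a missing keep-still sentence alone would be no finding. But the article publishes the scoring rule, and that rule, followed as written, credits execution to imagery. An instruction would reduce movement; it would not change how movement is scored when it happens.

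**The text does not treat execution as part of either condition.** MI excludes it by definition, the forearms rest on the stretcher, and section 3.3 speaks of target events, which implies some selection. That is fair, but none of it says how an epoch with real movement would be recognised or handled.

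**Stronger readings that the documents do not support.**

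- A reader might infer that any burst above threshold counts. It does not: the 100 ms minimum and the artefact step apply, although neither removes voluntary movement.
- A reader might infer that many participants will move, or that copying is confined to MI and AO. Section 2.3 permits residual function, but no figure shows how common it is or how often anyone would copy.
- A reader might take the 86% or 95% as the expected error. Those are the adverse end of assumed inputs, in a test that is not the plan's rule.

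**Restricting the main result to movement-free epochs would select on the response.** This also stands. Visible movement need not be voluntary copying, and section 5.1 is interested in a natural muscular response. Exclusion alone could discard genuine responses, so it should not replace the analysis of all epochs.

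**Conclusion.** The concern holds in a limited form. The stated event rule cannot distinguish covert activation from executed movement, while the article defines MI as excluding execution and attributes the scored activity to MI and AO. The direction of the bias follows from the design: upwards for MI and AO against control, and possibly towards an association with arm function.

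Its size is unknown, because the documents give no rate of movement. In the illustrative test, false activation runs from about 5% to 95% across the other tabulated scenarios. It falls to about 3%, close to the nominal 2.5%, when all four inputs are at their mildest together. The range shows that the problem may be trivial or decisive. Unless movement is marked at recording, the data cannot show which, since EMG amplitude alone does not reveal whether the hand moved. The change should be made, and it has to be in place before recording.

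**What to change.** 1. Give the same instruction in all three conditions: keep the arm relaxed and do not move the hand.
2. Have the person running the recording time-stamp any visible wrist or finger movement, with an event key or a camera on the hand.
3. Report the number of movers and the amount of marked time by condition.
4. Analyse the MI and AO response, and its association with arm function, twice: with all epochs, and with marked epochs excluded. Attribute activation to imagery or observation only if it persists without the marked epochs.

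**Cost.** One sentence of instruction, slight extra work for the operator, and fewer usable seconds in participants who move. Exclusion may drop some genuine involuntary responses, which is why both analyses are reported.

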### 3.4. Videos

Two recordings of identical durations will be available to compare the EMG recordings under each condition. Recording 1 will show images of landscapes without the presence of any person or animal and will be used for the control condition. Recording 2 will be based on the activities of the CEMIMA. In this recording, three activities will be visualised: opening and closing the hand, throwing and catching a tennis ball, pouring sugar into a coffee cup and stirring (Figure 1). The first minute of both recordings will serve as the resting time, which is essential for later analysis of the results. Recordings will be available in the open access repository for the research community once the study is finished.

## 4. Detailed Procedure

### 4.1. Experimental Conditions

The study participants will take part in three sessions, one session per week, and in each one, different experimental conditions will be used: experimental control conditions, experimental MI conditions and experimental AO conditions (Figure 2). In the first session, the socio-clinical-demographic data of all participants will be collected.

Recording 1 will be used during the control experiments and Recording 2 will be used in the MI and AO experiments (Figure 2); in the first case, the Spanish audio of the recording will be used, and in the second case, the images will be used. The first minute of both recordings will serve as a resting time, which is essential for subsequent analysis of the results.

During all three experiments, subjects will be seated in front of a stretcher on which they will rest their forearms with their elbows in slight flexion. Before the first experimental condition, socio-clinical-demographic data will be collected for the different assessment tools.

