### 3.2. Measurement Instruments

Degree of disability and dependence: Barthel Index. This is a generic measure that assesses the level of independence of the patient, allowing the degree of performance of the subject in some basic activities of daily living to be determined, assigning different scores and weightings. It is the most widely used scale internationally for the functional assessment of patients with an acute cerebrovascular pathology and its complications, such as vascular dementia. It includes 10 ADLs: eating, transferring between chair and bed, personal grooming, going to the toilet, bathing/showering, transferring (walking on a smooth surface or in a wheelchair), climbing/descending stairs, dressing, stool control, and urine control [16].Functionality of the upper limbs: Action Research Arm Test (ARAT). This test determines the functionality of the upper limbs after a cortical injury by assessing the ability to manipulate objects of different sizes, weights, and shapes with both hands. It consists of 19 tests divided into four subscales: gross grasp, grasping, pinching, and gross movement. The ARAT takes between 5 and 15 min to administer. It is a reliable and valid measure to assess the motor function of a person who has suffered a stroke. It also allows an assessment of spontaneous recovery and can detect changes that, after intervention, are in the range of clinically significant values [17].Cognitive impairment: Montreal Cognitive Assessment (MoCA). A valid instrument for assessing mild cognitive dysfunction. It consists of the following domains: attention, concentration, executive functions (including the capacity for abstraction), memory, language, visoconstructive abilities, calculation, and orientation. The maximum score is 30. A score of ≥26 is considered normal. Administration time: 10 min [18].Loewenstein Occupational Therapy Cognitive Assessment (LOTCA). This is a standardised occupational-therapy-specific test for use with stroke patients. The LOTCA consists of 20 subtests and assesses four areas: orientation, visual and spatial perception, visual motor organisation, and thinking operations. This test suite is consistent, internally valid, and reliable for determining an initial profile of the cognitive and perceptual abilities of the brain-injured patient [19].Mental evocation capacity: Mental Evocation of Images, Movements and Activities Questionnaire (CEMIMA). The questionnaire consists of two subscales: one of evocation and the other of sensation. It measures the ability to mentally form visual and kinaesthetic images of the hand/upper limb and can also be used to assess the imagination process of the person being assessed. A study of its reliability and validity determined it as an instrument that allows measurements of the ability to mentally form visual and kinaesthetic images of the hand/upper limb and allows an understanding of the imagination process of the person evaluated [20].Perception of quality of life: Stroke Impact Scala 16 (SIS-16). This is a self-report comprising 16 items from four physical domains (strength, hand function, mobility, and ADL/instrumental activities) included in the SIS 3.0. This facilitates its application, as it can be applied in a shorter time, in around 5–10 min [21].

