Another strength of this protocol is that it has taken into account certain aspects that have already been demonstrated in other studies. Repeatedly imagining different movements can lead to mental fatigue, affecting motor performance [36]. Therefore, it is essential to control the duration of the recordings and the number of movements and repetitions when designing protocols. In the case of AO, protocols and studies that have been carried out using EMG have shown that muscle activation occurs, and, after training, changes in the contraction of the muscles were studied [37,38]. However, these studies have not been conducted in the therapeutic field, so demonstrating that protocols of this type are effective may open doors in neurorehabilitation.

In terms of limitations, the main limitation may be the number of muscles evaluated, limited by the recording system to be used. It would be interesting to be able to record electromyographic activity in the contralateral limbs. Another limitation may be the convenience sample and its regional context. Furthermore, the heterogenicity of strokes could impact data generalisation. As it is an exploratory intervention, participants adherence can be influenced.

Finally, the analysis of the correlation between the electromyographic response by age may be limited by the smaller number of subjects expected due to the prevalence of stroke in those under 60 years of age.

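### Assessments that include the two-handed ARAT come before the first EMG recording in the same session, so one of the three conditions is recorded after use of the measured forearm muscles and the other two are not

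*Protocol article*

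**What the plan says.** Section 4.1 sets the visit structure: "The study participants will take part in three sessions, one session per week", with a different condition (control, MI or AO) in each. On the timing of the assessments it says "In the first session, the socio-clinical-demographic data of all participants will be collected" and then "Before the first experimental condition, socio-clinical-demographic data will be collected for the different assessment tools".

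Section 3.1 links the socio-clinical-demographic data to the first column of Table 1. That column includes upper-limb function and cognitive impairment. Section 3.2 measures the former with the ARAT, which works by "assessing the ability to manipulate objects of different sizes, weights, and shapes with both hands" over 19 tests, and the latter with the MoCA. Disability, cognitive-perceptual impairment, mental evocation and quality of life (Barthel, LOTCA, CEMIMA, SIS-16) stand in the second column.

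Section 4.2 places the EMG electrodes over the finger extensors and deep finger flexors of the forearm. Sections 3.4 and 4.1 reserve the first minute of each recording as rest. Section 3.3 counts contractile activity when the signal stays above the baseline mean by more than two standard deviations for 100 ms or longer. It also takes amplitude as ARV and RMS.

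**The concern.** The study compares EMG from the same muscles in the same people under three conditions. That comparison is clean only if the condition is the main thing that differs between recordings. Here a second difference is built in. One recording follows, on the same visit, a test in which the participant grasps, pinches and moves objects with the impaired arm. The other two recordings are made in later weeks, with no such testing described.

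The expected signal is small muscle activity in a seated participant who is imagining or watching. Residual activity or tiredness in the forearm after arm testing could be mistaken for a difference between conditions, or could hide one. Because the order is stated in the text, this is a feature of the design and not a detail left for a fuller document.

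**Working it through.** The plan gives no figure to reproduce, so the check is on the sequence, followed by a sum of stated times.

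**Step 1. Same session, assessments first.** Section 4.1 puts the data collection in the first session and before the first condition. With one condition per weekly session, exactly one of three recordings shares a visit with the assessments and follows them. No interval, rest period or separate assessment visit is given.

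**Step 2. Which tools are in that set.**
- ARAT: firm. Upper-limb function is in the first column of Table 1, which section 3.1 ties to the data named in section 4.1.
- MoCA: on the same footing, through cognitive impairment in that column. It is also needed for eligibility (section 2.3, score above 14), so some of it may be done earlier.
- Barthel, LOTCA, SIS-16 and CEMIMA: possible. Section 4.1 refers to the assessment tools without exception, and no other time point is given for any scale, but Table 1 lists these in the other column.
- CEMIMA has a further ambiguity. A secondary objective uses it as the MI tool during EMG, so it may belong to the MI session. If it is given in session 1, its content overlaps with the stimulus, since "Recording 2 will be based on the activities of the CEMIMA".

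**Step 3. Overlap of test and measurement.** The ARAT subscales cover grasping, pinching and gross movement with both hands, so the affected side is included. Grasp and pinch use the finger flexors and extensors, which are the muscles under the electrodes.

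**Step 4. Stated times (section 3.2).** ARAT: "The ARAT takes between 5 and 15 min to administer". MoCA: "Administration time: 10 min". SIS-16: about 5-10 min. LOTCA, Barthel and CEMIMA have no stated time.

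| Set given before the first recording | Minutes |
|---|---|
| ARAT alone | 5 to 15 |
| ARAT + MoCA | 5 + 10 = 15 to 15 + 10 = 25 |
| ARAT + MoCA + SIS-16 | 15 + 5 = 20 to 25 + 10 = 35 |

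If the whole set were given, the total would exceed the last row by an amount the article does not state.

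**Step 5. Does the rest minute remove the difference?** Each recording has its own rest minute, but in session 1 that minute falls after the testing as well. Two cases follow:
- If residual activity raises the baseline, the event threshold (baseline mean + 2 SD) rises and fewer events are counted in that condition.
- If residual activity fades during the video, the rest minute no longer represents the level against which later activity should be judged.

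ARV and RMS values that are not scaled to rest would carry the shift directly. The rest minute therefore protects only in part.

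**Step 6. Size.** The documents give no figure for how much prior arm use changes forearm EMG in this population, and the direction could go either way. No bias is computed here, because any number would only restate an assumption.

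**The case against.** The strongest reply is that the text supports much less than it may suggest. Several stronger readings are tempting, and the documents do not establish them:

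- **That the control comes first.** It is listed first in section 4.1, but the schedule is in Figure 2, which is not shown. The order may be fixed or varied.
- **That the full battery is run immediately beforehand.** The text says only before, and Table 1 splits the tools over two columns.
- **That the control is contaminated by imagery rehearsal.** This needs the CEMIMA to be given in session 1 and the control to be the first condition. Neither is certain. Any familiarity gained could also carry over to later weeks and would then not be confined to one condition.
- **That the control recording is the sole reference for MI and AO.** Each recording has its own rest minute, so a shift in resting tone in session 1 is at least partly absorbed and does not set the thresholds in the other sessions.
- **That the protocol concedes the point.** Section 5.1 says "Repeatedly imagining different movements can lead to mental fatigue, affecting motor performance". That concerns mental fatigue from repeated imagery, not muscle activity in someone seated in front of a video.

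All of this stands, and it limits the point to the ARAT and to an unquantified difference. It does not remove the point. The order of assessment and recording is stated, the ARAT is in the set, and the rest minute is taken in the same post-testing state. If the order is fixed, one condition differs systematically from the other two. If it is varied, the effect is spread over conditions as extra variation in a planned sample of 21 to 28.

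A further fair objection concerns the remedy. Moving the CEMIMA after the recording could mean that some participants complete it after MI or AO exposure and others before. Mental evocation is a predictor in the secondary objectives, so the remedy has to prevent this.

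**Conclusion.** The point holds in a limited form. By the protocol article's own sequence, one of three conditions is recorded after two-handed arm testing on the same visit, with no stated separation, and the other two are not. The conditions are therefore not recorded under like circumstances.

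The stated load is 5-15 min of arm testing, within 15-25 min of assessment if the MoCA is included and 20-35 min if the SIS-16 is too. Whether imagery on the CEMIMA also comes first is possible but open.

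The conclusion assumes that Table 1's first column defines what is collected before the first condition, as section 3.1 indicates, and that no unshown schedule inserts a rest or a separate visit. The size and direction of any bias are unknown. The change is worth making because it removes an avoidable difference almost for free, not because a given error rate has been shown.

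**What to change.** 1. In session 1, take the EMG recording first. Run the ARAT and all other scales not needed for eligibility afterwards. Keep only the eligibility MoCA before the recording.
2. Give the CEMIMA after the control recording and, for every participant, before any MI or AO exposure. If MI or AO can fall in session 1, fix one common CEMIMA timing for all participants so that the predictor stays comparable.
3. State in section 4.1 the order of conditions, which tools are given at which session, and the interval between testing and recording.

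Cost: one visit is reordered, with no added visit, time or staff. The downsides are that the scales follow a short seated recording and that CEMIMA timing must be coordinated with the order of conditions.
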